## Abstract

Although adult Huntington’s disease (HD) studies have significantly advanced our understanding of the course of degeneration, they may underrepresent critical neurodevelopmental aspects of the disease. Significant gaps remain in understanding how mutant huntingtin affects early neurodevelopment, its long-term impact, as well as potential implications for treatment outcomes. The Childhood to Adult Neurodevelopment in Gene-Expanded Huntington’s Disease (*ChANGE-HD;* NCT01951588) study aims to evaluate brain structure and function in premanifest, at-risk children and young adults, and explore HD’s developmental origins. Here, we introduce the ChANGE-HD study, which will investigate and integrate the neurodevelopmental and neurodegenerative aspects of HD. The ChANGE-HD study is a prospective, seven-year multi-site observational study with an accelerated longitudinal design, where participants are not bound to a fixed schedule across multiple visits. Four hundred and fifty participants aged 6–30 years who are at risk for HD will be recruited and asked to return for multiple visits (if possible). At each visit, cognitive, motor, behavioral, blood/saliva, and MRI data are collected. Alongside ChANGE-HD, we are also recruiting individuals for the juvenile-onset HD (JOHD) study to investigate the neuropathology of this rarer form of HD. ChANGE-HD represents the first prospective multi-site study to systematically document brain structure and function during the premanifest phase of HD in children and young adults. Data collection is ongoing with first results anticipated in 2026–2027. The ChANGE-HD approach is likely to provide novel physiological insights and guide the development of therapeutic strategies tailored to both the developmental and degenerative phases of the disease.

## Introduction

Huntington’s disease (HD) is an autosomal-dominant neurodegenerative disorder of the central nervous system (CNS) resulting from an abnormal trinucleotide repeat expansion of cytosine-adenine-guanine (CAG) in the Huntingtin (*HTT*) gene [1]. In the general population, the number of CAG repeats encoded within exon 1 of *HTT* ranges from 10 to 35. Repeat lengths between 36 and 39 demonstrate variable penetrance, whereas repeats exceeding 39 are classified as mutant *HTT (mHTT)*, resulting in HD with full penetrance.

*HTT* is a highly conserved gene essential for nervous system development, neuronal stability, and survival. The gene is maintained across species [2], suggesting that CAG repeats within *HTT* have undergone positive selection, potentially driving species survival through increasing CNS complexity. Notably, humans exhibit the highest number of CAG repeats, underscoring their unique evolutionary significance to the development of higher-order cognitive tasks [3–5].

Traditionally, HD has been viewed as a neurodegenerative disorder primarily affecting the striatum, characterized by motor, cognitive, and behavioral dysfunctions [6]. The prevailing explanatory hypothesis attributes the disease to a toxic gain-of-function mutation within *mHTT* (i.e., the CAG repeat expansion), resulting in neuronal damage and cell death. However, emerging stem cell, animal, and human neuropathological evidence suggests that brain development changes are critical to HD’s pathoetiology [7–9], raising the hypothesis that HD is an unintended outcome of an adaptive evolutionary process supported by a more functional CNS [3]. Thus, *mHTT*, in addition to causing pathological effects in adulthood, may positively affect the course of neurodevelopment. Understanding the complex interplay between neurodevelopment and neurodegeneration could transform treatment approaches, particularly by identifying critical inflection points where neurodevelopment transitions into degeneration. Most studies show that the degenerative process in HD begins roughly 20–25 years prior to onset [10–12]. These findings underscore the need to understand the effects of *HTT* on development, particularly in children and young adults at risk for HD.

### Lessons from Kids-HD

In 2009, the National Institute of Health (NIH) -funded Kids-HD study (ClinicalTrials.gov Identifier: NCT01860339) was launched at the University of Iowa, investigating the impact of *mHTT* on brain development in children at risk for HD [7]. For research purposes only, children aged 6–18 years-old at risk for HD (defined as having a parent/grandparent with HD) were genotyped and categorized as gene-expanded (i.e., GE, CAG >= 36) or gene-non-expanded (i.e., GNE, CAG < 36). The GNE children served as an excellent control group, given that being raised in an HD family can produce unique psychosocial strain not captured by children of non-HD families. A separate group of age-matched participants with no familial link to HD was also recruited as a comparison group. The Kids-HD study modeled the progression of HD several decades before the predicted age of motor onset in the GE participants. In total, we collected data from 406 individuals (13.73 ± 4.33 year; 177 Males, 227 Females; 2 unspecified) across 663 visits. Over the years, the Kids-HD study produced several key findings (Table 1). Some highlights include:

**Table 1 pone.0336088.t001:** Summary of Kids-HD papers/findings.

Clinical outcomes		
**Reference**	**Objective**	**Results/Conclusions**
Lee et al., 2018 [20]	Assess CAG effect on cognition in GE and GNE children aged 6–18 years.	*mHTT* has an inverted U-shaped effect on general intelligence (GAI): GAI scores increased and decreased with repeat length before and after 40–41 repeats, respectively, suggesting antagonistic effect of *HTT* on intelligence.
Tereshchenko et al., 2020 [21]	To determine the impact of *mHTT* on human measures of growth, including height, weight, and body mass index (BMI), between child and adolescent carriers of *mHTT* and control peers.	Decades before HD symptom onset, physical growth is abnormal in adolescent carriers of *mHTT*, suggesting that developmental aberrations may be systemic and a vital part of disease pathology.
Schultz et al., 2021 [14]	Evaluate the trajectory of cognitive skill development as a function of CAG repeat length in children and adolescents that carry the mutation that causes HD.	The development of verbal skills plateaus earlier as CAG repeat length increases.
Reasoner et al., 2022 [22]	Compare neuropsychiatric symptoms between child and adolescent huntingtin gene-mutation carriers and noncarriers	GE children had lower depression/anxiety compared to their peers. In contrast, GNE individuals largely show striatal volume growth. These findings suggest that lower depression and anxiety scores in GE children and adolescents may be associated with differential striatal growth.
Schultz et al., 2021 [23]	Compare crude markers of autonomic nervous system (ANS) function between GE children who were decades from their predicted motor onset and GNE children.	GE individuals 15–25 years before motor symptom onset have higher resting heart rate, systolic blood pressure, and core body temperature than their peers and GE individuals less than 15 years before onset. ANS dysfunction in HD seems to occur approximately 20 years prior to the predicted onset of motor symptoms of HD.
Byrne et al., 2017 [24]	Investigated whether neurofilament light protein (also known as NfL) in blood is a potential prognostic marker of neurodegeneration in patients with HD.	*mHTT* carriers have higher mean concentrations than non-carriers that increases across disease stages. NfL plasma concentrations were associated with clinical and MRI findings.
Neema et al., 2024 [17]	Investigate antagonistic pleiotropy in HD using a years-to-onset paradigm in a unique sample of children and young adults at risk for HD.	Decades from motor onset, GE participants show larger cerebral volumes and cortical features and significantly better cognitive, behavioral, and motor scores versus GNE controls. Greater brain size was associated with better behavioral performance in GE individuals.
**Neuroimaging outcomes**		
**Reference**	**Objective**	**Results/Conclusions**
Lee et al., 2017 [13]	Evaluate CAG effect on brain structure and function in healthy controls aged 6–18 years.	CAG repeats are positively and negatively associated with brain structure changes and higher IQ in females and males, respectively.
van der Plas et al., 2019 [15]	Evaluate brain growth trajectories in child and adolescent carriers of *mHTT* compared to peers without the mutation.	GE individuals have greater striatal and pallidal volume compared with GNE, suggesting atypical brain development. CAG repeat length is positively correlated with early life striatal volume and a steeper slope of decline later in life.
Tereshchenko et al., 2020 [25]	Compare functional connectivity between the striatum and cerebellum in GE and GNE children at risk for HD.	Striatal-cerebellar resting state functional connectivity is greater in GE compared to GNE between in individuals 6–12 years old and continues to decline linearly afterwards.
Reasoner et al., 2022 [16]	Evaluate the impact of *mHTT* on the developmental trajectories of cortical thickness and surface area.	Cortical, but not striatal, volume is similar between GE and GNE individuals across age and not affected by CAG repeat length.

***HTT* impacts brain structure and function along the entire spectrum of repeats**: Higher repeats are associated with better cognitive skill and greater brain volume in GE and GNE individuals [13,14].**Methodological challenges of modeling age and CAG separately, versus years-to-onset model (which incorporates both):** The Kids-HD study employed an accelerated longitudinal design (ALD), the gold standard for evaluating brain development in children, which combines cross-sectional and longitudinal data to model age-related changes across a broad developmental window. This model showed not only interesting findings of accelerated striatal development, where GE children reached peak striatal volume years before the GNE group, but that these trajectories were profoundly affected by CAG repeat length [15]. We also found that every CAG repeat conferred a greater advantage in general cognitive ability [14]. This effect peaked at repeats of 43 and individuals with longer CAG repeats showed trajectories that were declining in function after age 15, likely representing changes due to the degenerative phase of the disease. The age-trajectory modeling results highlighted the profound consequences *HTT* and CAG repeat-length has on neurodevelopment. These findings recapitulate the well-established negative relationship between CAG repeat length and age of motor onset and require an updated model to take both factors, and their interactions, into account. Given the influence CAG repeats and age exert on longitudinal brain development, we began modeling the data in a Years-To-Onset (YTO) fashion to evaluate the time course of the disease from development to degeneration. The YTO model predicts the age of motor onset based on the participant’s current age and CAG repeat length. Importantly, the YTO model can reveal information about disease trajectory that is obscured when plotting data by age. For example, Reasoner et al. (2022) found that cortical volumes are similar across age groups [16], while Neema et al. (2024) found evidence for higher and lower cortical volumes depending on the YTO of the individual [17]. The critical difference between approaches is that while higher age and lower YTO both predict decline in cognitive and motoric function, age-only models ignore variability in disease trajectory caused by CAG repeat length. An example of the difference between an age-only trajectory and a YTO model is as follows: An 8-year-old with a CAG repeat length of 48 and a 22-year-old with a CAG length of 43 both have 26 YTO, despite being on opposite ends of the age trajectory model. Thus, potential differences in cortical volumes could have been missed by Reasoner et al. (2022) because participants at similar ages were at different points in their disease trajectory. Additionally, when evaluating a biomarker of degeneration in Kids-HD (neurofilament light; “NfL”), we found that NfL levels are normal as far back as 40 YTO but rise around 20 YTO [18]. These findings support the notion that the YTO model can accurately characterize the developmental phase of the disease process, which occurs 20 years before the onset of motor symptoms.**The antagonistic pleiotropy theory of *HTT* and its implications for neurodevelopment:** In our most recent publication, we revealed that GE individuals from 50−20 YTO have larger cerebral volumes, more cortical surface area, and higher IQs compared to GNE subjects, but the opposite is true after 20 YTO [17]. Striatal and pallidal volumes remain comparable in volume to GNE until 20 YTO after which they dramatically decline in volume, consistent with early vulnerability of the basal nuclei. These findings challenge the traditional concept of HD as a uniquely neurodegenerative disorder and highlight the neurodevelopmental role of *mHTT.* Additionally, Kids-HD research uncovered potential early advantages of *mHTT* in GE children, such as larger brain development that supports enhanced cognitive development and reduced depression/anxiety. However, these children will indeed develop HD, highlighting the yoking of advantage with disadvantage. Our findings support the notion of antagonistic pleiotropy in HD, where the same neurodevelopmental differences that confer early advantage eventually lead to vulnerability and subsequent degeneration [19]. Collectively, they reshape our understanding of the evolutionary implications of *mHTT* and its potential role in brain development

### Beyond Kids-HD: Embracing a new era with ChANGE-HD

While the Kids-HD study provided novel insights, it also raised several critical questions that required further investigation. Kids-HD’s modest single-site sample (202 GE children) produced valuable data but required a necessary expansion for greater reliability and broader application. This prompted the launch of the NIH-funded, multi-site ChANGE-HD study in 2019, which builds upon the Kids-HD findings and addresses the following key areas:

**Expansion and Replication:** No single study can provide definitive conclusions. ChANGE-HD aims to reproduce the Kids-HD findings using a larger sample size across multiple sites to ensure more robust, generalizable data.**CAG-specific effects:** Kids-HD identified CAG-specific effects in the GE group, where different repeat lengths produce distinct neurodevelopmental trajectories. To fully understand these effects, ChANGE-HD will recruit a larger cohort to enable a thorough analysis across a fuller range of repeats.**Wider age range amongst participants:** Kids-HD originally recruited participants from age 6 through age 18, but maturational changes extend into late 20s and early 30s [26]. Although YTO models address the strict need for sampling participants across a broad spectrum (as demonstrated by the example above), it is still beneficial to examine older participants who are approaching their date of motor onset to better model trajectories at low YTOs.**Evaluation of serum biomarkers of disease progression – NfL:** Serum NfL is a marker of neuronal damage in premanifest HD (among other neuronal diseases and disorders), with levels rising approximately 15–20 YTO, and is strongly correlated with the age of motor onset. Although NfL is classically absent in the developmental phase and appears after the onset of subtle neurodegeneration, its use as a biomarker for HD remains unclear and requires further investigation. The CHANGE-HD study aims to clarify the trajectory of NfL in younger at-risk individuals and explore its relationship with clinical outcomes and MRI findings.**The ChANGE-Juvenile Onset Huntington’s disease (JOHD) Study:** Expanding our sample size across multiple investigation sites allows us to delve deeper into the 5–10% of HD cases where symptom onset occurs before the age of 21, or JOHD [27–29]. Therefore, along with studying adolescent and adult-onset HD, we have included a companion study of ChANGE-JOHD where we will investigate the neuropathology of this rarer and more aggressive form of HD. This study will leverage the infrastructure of the ChANGE-HD study and follow a similar protocol.

The study also seeks to expand on other HD-related studies, such as TRACK-, PREDICT-, IMAGE-HD, and HD-YAS. Beyond the fact that we are studying a population that is much further from the possibility of disease manifestation, ChANGE-HD has other distinctions. First, whereas TRACK-, PREDICT-, and IMAGE-HD examined the disease from the earliest point of neurodegeneration and just prior to cortical and subcortical volumetric atrophy, the ChANGE-HD study focuses on developmental alterations in neural connectivity and structure, with the hypothesis that *mHTT* confers a pre-manifest benefit to inheritors. Second, whereas other studies have sought to determine the earliest potential time for interventions we seek to determine whether there is a point where early intervention may be detrimental. Third, we expand on HD-YAS by determining whether increases or decreases in cellular stress markers, such as NfL can be observed during the neurodevelopmental phase of the disease. Fourth, our broad toolbox of instruments has been updated to include more sensitive measures that can capture performance variability in individuals < 10 years old, such as the Q-Motor test, which relies on force transducers, rather than observation, to quantify motor system function [30]. In addition to self-reports, ChANGE-HD also extends beyond these studies by recording participant data from parents’ reports as well. Lastly, our neuroimaging protocols have been updated to conform to other large-scale studies of children and adolescents (see *Magnetic Resonance Imagine* section below) [31]. We note that although ChANGE-HD is distinct in many ways, we maintain several measures used in previous studies, such as the core neuroimaging scans to measure neural volume (including T1 and T2-weighted scans), verbal fluency tests, CAG repeat length assessments, and NfL quantification.

The goal of ChANGE-HD is to model development (versus degeneration) by focusing on individuals whose brain changes likely reflect neurodevelopment rather than disease progression. The broader objectives include:

**Using structural and functional MRIs to monitor brain development over time**. A specific focus is given to striatal circuitry, due to its centrality to HD and its prominence in earlier data.**Evaluate the relationship between brain structure and cognitive, behavioral, and neurologic assessments**. Here, we aim to elucidate the precise effects of *mHTT* on cognition.**Investigate the link between CAG repeat length and clinical (motor scores, cognitive evaluations etc.) and biological (neuroimaging, biomarkers) measures**. This includes evaluation of NfL as an appropriate marker of neurodegeneration in HD.**Investigate the putative roles of genetic variants on development.** CAG repeat length is the most significant driver of symptom progression in individuals with *mHTT*. However, there still exists variation in the age of motor onset in individuals with similar CAG repeat lengths. This fact has motivated genome-wide association studies to identify variants that delay (e.g., *FAN1*) or accelerate (e.g., *MSH3*) the age of motor onset in patients with HD [32–34]. Several of the identified variants exist on genes implicated in DNA repair [33,35], ultimately exacerbating or preventing somatic instability. While these genes are typically studied in the context of HD neurodegeneration, several play a role in disorders associated with altered neurodevelopment, such as schizophrenia and autism [36], and HD and muscular dystrophy [35]. Using blood or saliva samples obtained at each visit, we will explore whether these genetic variants accelerate or delay development.

The study objectives will be achieved by improving upon the Kids-HD infrastructure, including adding more study sites and adding more precise measures (e.g., Q-Motor). We expect the study to validate pre-manifest biomarkers of neurodegeneration and their relationship with the age of motor symptom onset. We also expect to reveal novel and potentially opposite effects of these biomarkers on neurodevelopment:

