### Power analysis and sample size calculation

Based on our findings from the Kids-HD sample, our central hypothesis is that GE participants will demonstrate altered trajectories in general brain size and cognition across YTO. Specifically, we predicted that GE individuals will demonstrate significantly larger brain volume (primary outcome measure) and stronger cognition scores (secondary outcome measures) prior to 20 YTO and significantly smaller brain volume and weaker cognition between 20−0 YTO. Using our updated recruitment target of 1,030 assessments across 450 participants, we estimated at least 90% power to reproduce our previous findings at p = .01 (except for cortical thickness; Table 5). Note that Table 5, which shows the results of our power analysis, includes functional and structural measures, but that our power analysis is primarily based on the structural findings from Kids-HD. Assuming 40% of participants are GE (as in the previous study), we can assume at least 400 visits from 180 unique genetically affected participants. The power analysis used the Kids-HD sample from Neema et al. (2024), and was based on 136 visits from 79 gene-expanded participants. Because the mean number of visits (and hence, statistical information) per participant will be higher in ChANGE-HD, a conservative estimate of the overall increase in statistical information (i.e., log-likelihood statistics) is obtained from the ratio of unique participants, which is 2.278. If the findings from Kids-HD hold, then the expected values of the analogous F statistics (Table 5) will increase by at least 2.278-fold. Standard power calculations using these projected F statistics yield results that exceed the above-claimed minimum statistical power.

**Table 5 pone.0336088.t005:** Tests used for hypotheses and power analysis (from Neema et al., 2024).

		Kids-HD				Change-HD		
**Measures**	**N**	**ndf**	**ddf**	**F**	**p**	**Projected F**	**Projected NCP**	**Power**
General Ability Index**	136	1	87.66	13.50	<0.001	30.78	29.445	0.997
Behavior composite**	135	2	120.27	10.91	<0.001	24.87	47.343	>0.999
PANESS**	128	1	46.12	8.92	0.005	20.34	18.933	0.956
Whole brain*	117	3	62.63	7.79	<0.001	17.76	49.491	>0.999
Cerebrum	117	3	62.55	7.80	<0.001	17.78	49.557	>0.999
Cortical gray matter*	117	1	99.90	12.22	<0.001	27.86	26.593	0.995
Cortical surface area	117	1	95.22	12.17	<0.001	27.75	26.468	0.994
Cortical thickness*	117	1	54.67	2.95	0.091	6.73	5.612	0.406

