To assess the relationship between age- and sex-adjusted neuroimaging variables (e.g., cortical grey and white matter volume, striatal volume, corticostriatal structural and functional connectivity, etc.) and clinical outcomes in GE individuals, we apply modeling techniques as described above. The models include random effects of subject and family, but exclude age and sex, as the values will have already been corrected using the data from GNE participants. Imaging measures are generally predictor variables, and clinical measures are the outcomes, reflecting the potential causal relationships between the two measurement classes. As in our previous work [17], we also split our GE participants into two groups with a cutoff of 20 YTO and test for differences in the imaging versus clinical relationships. This is based empirically on our work [17] showing divergence in neural and behavioral measures at this point in the YTO trajectory and because of work showing an upward trend in NfL at 20 YTO [18]. As described above, potential non-linear relationships between biomarkers and clinical measures are interrogated using restricted cubic splines (up to five degrees of freedom). For all analyses, a *p* value of < 0.05 is considered statistically significant.

In addition to our hypothesis-driven analyses, we also plan to perform detailed exploratory analyses to uncover novel neuroimaging biomarkers that both distinguish GE and GNE individuals and individuals with variations in HD-related single nucleotide polymorphisms (SNPs). For example, machine learning approaches, such as deep learning, have been applied to neuroimaging data from patients with neurodegenerative disorders to identify how those SNPs affect brain anatomy and function [81]. As mentioned above, SNPs in several genes explain variation in the eventual onset of motor symptoms in HD [32–34]. Using deep learning and other machine learning approaches as exploratory tools may reveal new mechanistic information about how these SNPs shape neurodevelopment and -degeneration.

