Be diagnosed with JOHD by a trained neurologist prior to the age of 21, based on motor symptomology (the participant’s genetic status is confirmed after consent is obtained).Be between 6–30 years old at baseline. Thus, even though the diagnosis is made prior to 21, assessment for the study is not restricted to ages under 21.Not be bed-ridden, unable to communicate, or beyond travel conditions that are too strenuous for the individual.

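### Former Kids-HD participants can enter the ChANGE-HD tests unmarked, although those tests are meant to reproduce Kids-HD; a coded flag and a companion analysis without them would protect the replication claim

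*Protocol article*

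**What the plan says.** Replication is a stated aim. Under Beyond Kids-HD, the article says that "ChANGE-HD aims to reproduce the Kids-HD findings using a larger sample size across multiple sites". The section on power analysis and sample size opens with "Based on our findings from the Kids-HD sample, our central hypothesis is that GE participants will demonstrate altered trajectories". It predicts larger brain volume and stronger cognition before 20 YTO, and the reverse from 20 to 0 YTO. The power inputs in Table 5 come from 136 visits by 79 GE Kids-HD participants.

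For the imaging-clinical relationships, the section Statistical analysis using YTO Models says "we also split our GE participants into two groups with a cutoff of 20 YTO". It justifies the cutoff this way: "This is based empirically on our work [17] showing divergence in neural and behavioral measures at this point in the YTO trajectory". The second justification there is neurofilament light, which the introduction also reports as a Kids-HD result: "we found that NfL levels are normal as far back as 40 YTO but rise around 20 YTO".

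The Participants section lists age 6 to 30, English fluency, a parent or grandparent with HD and an age-appropriate understanding of HD, followed by the exclusions. Neither that list nor the stepwise analysis mentions earlier participation in Kids-HD. The article does not say that the two samples are independent, and it does not say that they overlap.

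**The concern.** A replication is persuasive because the new data had no part in suggesting the hypothesis. Here the hypothesis, its direction and one cutoff were taken from Kids-HD, and the design leaves room for the same people to appear again.

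- **Risk definition.** Kids-HD studied "children aged 6–18 years-old at risk for HD (defined as having a parent/grandparent with HD"), which is the same family-history rule as in ChANGE-HD.
- **Site.** Kids-HD was a single-site study that "was launched at the University of Iowa, investigating the impact of" the mutation on brain development. Iowa is also the primary ChANGE-HD site and the largest contributor in Table 4, with 302 of 1,004 (30%).
- **Age.** A participant aged 18 in 2009 was about 28 in 2019, still inside the 6 to 30 range.

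Brain volume differs persistently between people. If the Kids-HD participants happened by chance to have a favourable pattern, those who returned would bring part of it with them. The subject and family random effects in the models handle repeats and relatedness within ChANGE-HD, but not dependence on the earlier study. The stakes are set out in the Discussion: reproducing the early advantage would be used as a caution against lowering mutant huntingtin early in the disease.

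**Working it through.** **1. The plan's own figures.** Inputs from the power section: 450 participants × 40% GE = 180 GE; 79 GE in the Kids-HD analysis; ratio 180/79 = 2.278, as printed. For cortical gray matter (F = 12.22, 1 and 99.90 df):
- projected F = 12.22 × 2.278 = 27.84 (printed 27.86);
- non-centrality = (27.84 − 2 × 27.84/99.90 − 1) × 1 = 26.29 (printed 26.593);
- power at alpha 0.01 from the non-central chi-square = 0.995 (printed 0.995).

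All 15 power values in Table 5 reproduce to within 2 percentage points. The stated power is not in question.

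**2. Effect of returners if there is no true effect.** Let k of the 79 return among the 180, and let ρ be the correlation between a person's contributions to the two studies. Treating each test as a person-level mean, the correlation between old and new test statistics is c = ρk/√(79 × 180) = ρk/119.25. Given an old z of 3.5 (√12.22 = 3.50), the new z has mean 3.5c and variance 1 − c². The chance of a same-direction result at two-sided 0.05 is P(Z > (1.96 − 3.5c)/√(1 − c²)).

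Neither k nor ρ is in the document. Both are assumed, with ranges shown.

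| k | c (ρ = 0.5) | chance | c (ρ = 0.9) | chance |
|---|---|---|---|---|
| 0 | 0 | 2.5% | 0 | 2.5% |
| 20 | 0.084 | 5% | 0.151 | 7% |
| 40 | 0.168 | 8% | 0.302 | 17% |
| 79 | 0.331 | 20% | 0.596 | 56% |

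At the stricter 0.01 level used for the power analysis, the two-sided chances are 1.3-2.0%, 2.2-5.6% and 6.7-27.1% for k = 20, 40 and 79, against 1% with no overlap.

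**3. Power without flagged GE participants.** Replace 180/79 by (180 − k)/79, where k is now the number of GE participants removed, and repeat step 1 at alpha 0.01. For cortical gray matter with k = 40: ratio 140/79 = 1.772, F = 21.66, non-centrality 20.22, power 0.97. With k = 79: ratio 101/79 = 1.278, F = 15.62, non-centrality 14.31, power 0.89.

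| Outcome | k = 0 | k = 20 | k = 40 | k = 79 |
|---|---|---|---|---|
| Whole brain | >0.99 | >0.99 | 0.998 | 0.975 |
| Cerebral white matter | >0.99 | >0.99 | >0.99 | 0.996 |
| Cortical gray matter | 0.995 | 0.988 | 0.973 | 0.886 |
| General Ability Index | 0.998 | 0.994 | 0.984 | 0.920 |
| PANESS | 0.957 | 0.928 | 0.881 | 0.716 |
| Thalamus | 0.917 | 0.874 | 0.812 | 0.624 |

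Cortical thickness is at 0.41 with the full sample, so it is underpowered in any case.

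**The case against.** The strongest objection is that the point rests on silence. The article reports no returner, and a condensed article may leave the handling of returners to the full protocol or analysis plan. That stands as far as the facts of overlap go, and it limits the point to a conditional one. It does not remove it: the article prints an eligibility list and a stepwise analysis, and on those terms every eligible person enters the tests offered as reproducing Kids-HD.

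A reader might go further and infer that the replication is circular. The documents do not support that, for these reasons:
- Overlap is not documented.
- Kids-HD had 202 GE children, and only 79 GE participants fed the source analysis. A GE returner need not be one of them, and the other 123 would carry less, if anything, of that result.
- Non-expanded returners enter only the age and sex correction. Repeats of 36-39 and above 70 are left out of the YTO analysis, and overt motor features bar enrolment.
- The primary test is the overall YTO effect, which does not use the 20-YTO cutoff. The split belongs to the imaging-clinical analysis. The introduction also cites other studies that place the start of degeneration 20-25 years before onset.

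The 56% figure should not be quoted alone. It needs all 79 to return and a correlation of 0.9, despite intervening development and a move from one Siemens scanner to three vendors (General Electric at Iowa). The test is of a YTO trajectory, so each person's shift along YTO may lower the correlation further. Whole brain and white matter are 3-df tests, to which the same-direction calculation does not apply directly. The main cognitive battery has changed from the Wechsler scales to the NIH Toolbox, which weakens the carry-over there.

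**Conclusion.** The point holds in conditional form. The printed plan does not separate former Kids-HD participants from new ones in tests whose hypothesis, direction and power inputs came from Kids-HD. With no returners from the 79, nothing is lost. With 20, the effect is small: about 5-7% against 2.5%. It becomes serious only if a large share came back: 8-17% with 40, and 20-56% at the extreme. These figures assume no true effect, a 1-df outcome with Kids-HD z = 3.5, a within-person correlation of 0.5 to 0.9, and a test that behaves like a person-level mean. Neither the number of returners nor the correlation can be learned from the article. This is an inexpensive safeguard for the replication claim, not an error in the stated power or in the primary model.

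**What to change.** Carry a coded flag for any prior Kids-HD participation. It should hold no genetic status, so that blinding is unaffected, and the number flagged should be stated. Prespecify that the primary-outcome YTO tests and the 20-YTO contrast are also reported without flagged GE participants, as a companion to the full-sample tests and not a replacement. Let the word replication rest on agreement between the two.

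The work is one variable and one extra set of model runs. The price is precision in the companion analysis if many returned: power for cortical gray matter at alpha 0.01 is about 0.97 with 40 GE participants removed and 0.89 with 79, while PANESS and the thalamus fall below 0.90 by 40. Because the flag covers all of Kids-HD and not only the 79, it could remove more GE participants than strictly necessary, and the loss would then be larger.
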